### Clinical evaluation and characterization of the sample

Before performing the experimental protocols, the participants will be submitted to the following evaluations: anamnesis, conventional 12-lead ECG and treadmill clinical exercise test, performed in the presence of a cardiologist, assisted by a physiotherapist. The aim of these tests will be the clinical and cardiovascular evaluation of the participants.

To characterize the participants and verify their health status, the following evaluations will be performed before the experimental protocol: body composition evaluation by dual-energy x-ray absorptiometry (DXA) (Discovery DXA System, Hologic, USA), nutritional assessment and blood tests (lipid profile, total cholesterol, high density lipoproteins (HDL), low density lipoproteins (LDL), urea, creatinine, fasting glucose, uric acid, insulin resistance, C-reative protein and glycated hemoglobin, to check their health status.

### Experimental protocol

The experimental protocol will take place over 13 weeks, as shown in Fig. 1. In the 1st, 5th, 9th and 13th weeks, the participants will be submitted to the following evaluations: CPET, RMS, iIME and constant load test (CLT). The PFT will be performed only in the 1st and 13th weeks of the study. The IMT will be carried out for 11 weeks. It is emphasized that the participants will continue doing the training during the reevaluation weeks. The aim of the reevaluations, which will be carried out in the 5th and 9th weeks of training, is to readjust the training loads and to follow the responses to the IMT.

**Fig. 1 Fig1:**
[figure not shown]
Template of recommended interventional trials (SPIRIT) schedule. 60G, 60% of maximal inspiratory pressure group; CLT, constant load test; CPET, cardiopulmonary exercise test; iIME, incremental inspiratory muscle endurance test; CPG, critical inspiratory pressure group; PFT, pulmonary function test; RMS, respiratory muscle strength test; SG, sham group; sham, 6 cmH_2_O

### Respiratory muscle strength tests (RMS)

The evaluation of RMS will be performed with the participants at rest in the sitting position, using a digital manovacuometer (MVD-300, Globalmed, Porto Alegre, Brazil) and a nasal clip, according to the Brazilian guidelines for measuring maximal static respiratory pressures [36]. This measure will always be carried out by the same appraiser.

MIP will be determined after maximal inspiratory effort, from the residual volume. The MEP will be determined after maximal expiratory effort, from total lung capacity. These maneuvers will be performed against a rigid tube, occluded distally and a 2-mm-hole mouthpiece [36] will be used. The values of the maximal respiratory pressures will be those observed in the first second after the peak of pressure [36]. At least three maneuvers will be performed, with a 30-s interval between each maneuver [37], obtaining the highest reproducible values (difference < 10%) found in at least three maneuvers and considering the maximal respiratory pressure as the highest value. Normal values will be based on the regression equation proposed by Neder et al. [38] for the Brazilian population. Respiratory muscle weakness, maximal static pressure values < 60% of those predicted, will be considered [33].

### Cardiopulmonary exercise test (CPET)

The CPET will be used to assess the aerobic power of the participants’ VO_2 PEAK_ [39] to determine the gas exchange threshold (GET) by the ventilatory method [40], the respiratory compensation point (RCP) [39] and inspiratory muscle metaboreflex [41].

A ramp-type protocol will be performed on an electromagnetic braking cycle ergometer (Corival V3, Lode BV, The Netherlands) and will consist of a 6-min rest, 3-min free-load warm up (0 watts) and a gradual increase in load until the exercise is stopped, followed by 6 min active recovery (25 watts) and 1 min passive (without pedaling) recovery. The power increment will be calculated for each participant according to the values established by the formula described by Wasserman et al. [42] and adapted according to the evaluator’s experience, preventing the increment from being underestimated.

Participants will be instructed to maintain a cadence between 60 and 80 rpm throughout the protocol and the test will last from 8 to 12 min [42]. Three independent evaluators will determine the GET and the RCP. The highest value of VO_2_ obtained in the last 30 s of the CPET will be considered the VO_2PEAK_ [39]. In addition, the following variables will be evaluated in the GET and peak effort: VO_2_, VCO_2_, VE, OUES and VE/VCO_2_ slope [39, 43].

The activation of the inspiratory muscle metaboreflex will be evaluated by analyzing the patterns of the variables: O_2_Hb, HHb and tHb obtained by near infrared spectroscopy (NIRS) and the cardiovascular data, HR and mean arterial pressure (MAP), obtained by a bioamplifier for ECG signals (BioAmp FE132) and a Finometer (Finapres Medical Systems, The Netherlands), respectively, at the intensities of 50–100% of the VO_2PEAK_, subdivided into 10% intervals. In addition, the activation point of the inspiratory muscle metaboreflex will be considered the moment at which the nonlinear HR, MAP and oxygenation decrease for the vastus lateralis (VL) and increase for the external intercostal (EI), i.e., redirection of blood flow from the peripheral musculature to the respiratory muscles [6].

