#### Primary outcome measures

The primary outcome measure is the performance on exercise: peak oxygen uptake (VO_2PEAK_) and work load (W) were obtained by cardiopulmonary exercise testing (CPET).

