### Subjects

Thirty recreational male cyclists, aged between 20 and 40 years, will be evaluated. They will be randomly divided into three groups: sham group (SG), PThC group (CPG) and 60% of the MIP group (60G). The groups will be formed by the randomization of the paired individuals with the same aerobic functional classification [31] and age group (subdivided into decades), using R software 3.0.2 to allocate the subjects.

The criteria used to select the participants will be as follows: male subjects aged 20 to 40 years old, apparently healthy, who have been practicing cycling for at least 6 consecutive months and at least 150 min/week (classified as active by the American College of Sports Medicine [32]). In addition, participants must not have abnormalities in the cardiovascular, respiratory, musculoskeletal or neurological systems, nor of other systems that make the proposed tests impossible. The exclusion criteria of the study are as follows: participants with electrocardiogram (ECG) changes (ischemia, overload, severe arrhythmias (such as ventricular tachycardia) and conduction disorders), both at rest and during the clinical exercise test, obesity (body mass index (BMI) >30 kg/m^2^), diabetes mellitus, hypertension, alterations in the results of laboratory tests, participants with respiratory muscle weakness (MIP<60% predicted [33]), smokers or former smokers with at least 1 year of interruption, alcoholics and users of illicit drugs or medication that may interfere with the results of the research and participants who have performed some type of IMT the last 12 months.

The participants will be recruited by electronic and printed media and by contact with subjects included in the database of the Laboratory of Cardiovascular Physiotherapy (LFCV) at the Federal University of São Carlos (UFSCar). Once identified, eligible participants will be invited to participate in the study and after they have accepted, they will carry out all the evaluations described subsequently and the type of training to which they are allocated.

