### Metabolic and respiratory variables

The ventilatory and metabolic variables will be collected, breath by breath, through a system of expired gas measurements (Ultima MedGraphics - St. Paul, MN, USA) and processed using specific software (Breeze Suite 7.1, MedGraphics - St. Paul, MN, USA). In addition, the BORG/CR10 scale [35] will be used to assess the participant’s subjective perception of the exercise.

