#### Statistical analysis

Due to the lack of studies that evaluate the effect of different loads of IMT, among them PThC, on the physical performance in recreational cyclists, we chose to carry out the statistical analysis considering the desired study effect size as proposed by Cohen [48]. Thus, the sample calculation was performed using GPower software 3.1.3 to determine the sample size, the mean effect size (*f* = 0.25, according to Cohen [48]) was used for the two-way mixed analysis of variance (ANOVA) and values of 0.05 for the type I probability error (α) and 0.80 for the type II probability error (power or β). Therefore, in order to ensure these pre-established conditions, at least 30 subjects should participate in this study.

All statistical analyses will be processed using the SPSS Statistics software 17.0 (SPSS Inc., Chicago, IL, USA). The level of significance will be set at *p* < 0.05. Normally distributed data will be presented according to the mean ± standard deviation and non-normally distributed data according to the median (interquartile range).

The Shapiro-Wilk test will be used to test for normal distribution and the Levene test for evaluation of homogeneity. A descriptive analysis of the three groups evaluated and then the paired *t* test will be performed on the following data: age, anthropometric evaluation, body composition densitometric analysis and blood test results.

The three groups will be compared considering the factors of group and training time, in terms of the variables PFT (FVC, FEV_1_/FVC, IC, ERV and MVV), RMS (MIP and MEP), CPET (VO_2PEAK_, VE, RR, OUES and VE/VCO_2_slope), cardiovascular variables (HR, CO, SAP, SV, total PVR) and metabolic variables (O_2_Hb, HHb, tHb and VO_2PEAK_), using two-way mixed ANOVA for parametric data analysis and for non-parametric data analsysis, the data will be mathematically transformed in order to normalize the data.

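### VO2peak, a primary outcome, is the highest value in the last 30 s rather than a 30-s mean, with no averaging interval stated; the main cost is lost precision

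*Protocol article*

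**What the plan says.** The section Primary outcome measures names two exercise measures: "peak oxygen uptake (VO_2PEAK_) and work load (W) were obtained by cardiopulmonary exercise testing (CPET". The section Cardiopulmonary exercise test (CPET) gives the rule for the first: "The highest value of VO_2_ obtained in the last 30 s of the CPET will be considered the VO_2PEAK". The same section describes a ramp that rises until exercise stops, followed by active and passive recovery as part of the test.

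Under Metabolic and respiratory variables, the article states how the values arise: "The ventilatory and metabolic variables will be collected, breath by breath, through a system of expired gas measurements". It adds that they are "processed using specific software (Breeze Suite 7.1, MedGraphics - St. Paul, MN, USA". No averaging interval, filter or rule for outlying breaths is given. Nothing says that the peak is read from unaveraged breaths either.

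The CPET is done in weeks 1, 5, 9 and 13 (Experimental protocol). The Statistical analysis section bases the sample size on a generic f of 0.25 for a two-way mixed ANOVA and concludes that "at least 30 subjects should participate in this study". It gives no SD or repeatability figure for VO2peak.

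**The concern.** The highest of several noisy values lies above the underlying level on average, and it varies more from test to test than their mean. Breath-by-breath VO2 is noisy, so a rule that picks the top value in a 30-s window keeps noise that averaging would remove. The article states this estimator for a primary outcome, so it is a choice and not merely an omitted detail.

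The trial is small: 30 men in three groups, or 10 per group if allocation is equal. Extra within-person noise in VO2peak works directly against the group-by-time comparison. The same stored data could give a more repeatable value at almost no cost.

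**Working it through.** **1. The plan's own figure.** Inputs from the article: f = 0.25, alpha 0.05, power 0.80, k = 3 groups, m = 4 CPETs. Assumed because not given: correlation 0.5 between visits and sphericity. For the interaction, λ = f²·N·m/(1−ρ) = 0.0625 × 30 × 4 / 0.5 = 15, with (3−1)(4−1) = 6 and (30−3)(4−1) = 81 degrees of freedom. Power is 0.809, so N = 30 reproduces. With three time points the same formula gives 36, and with two it gives 42.

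**2. Raw breaths.** Assume n independent normal breaths in the window with SD s. The maximum has a known mean excess and SD; the 30-s mean has SD s/√n.

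| n | excess of maximum | SD of maximum | SD of mean | SD ratio |
|---|---|---|---|---|
| 20 | 1.87s | 0.525s | 0.224s | 2.35 |
| 25 | 1.96s | 0.508s | 0.200s | 2.54 |

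The noise-variance ratio is therefore 5.5 to 6.5. Letting n run from 15 to 30 and allowing a lag-1 correlation of 0 or 0.3 between breaths gives SD ratios of 1.7 to 2.7.

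**3. If the software averages first.**
- Three 10-s bins: the highest has SD 0.748 bin SD, against 1/√3 = 0.577 for their mean. The ratio is 1.30 and the excess is 0.85 bin SD.
- Two 15-s bins: 0.826 against 1/√2 = 0.707. The ratio is 1.17.

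**4. Effect on precision.** Illustrative assumptions: n = 20, breath-to-breath CV 5%, other day-to-day SD D of 3% or 4%, and f = 0.25 taken to apply to the 30-s mean. The mean has SD 5/√20 = 1.12%. The raw maximum has SD 0.525 × 5 = 2.62%.
- D = 4%: variance ratio (16 + 6.89)/(16 + 1.25) = 1.33; λ = 15/1.33 = 11.3; power 0.67.
- D = 3%: (9 + 6.89)/(9 + 1.25) = 1.55; λ = 9.7; power 0.59.
- 10-s bins (SD 1.30 × 1.12 = 1.45%): ratios (16 + 2.10)/17.25 = 1.05 and (9 + 2.10)/10.25 = 1.08; power 0.79 and 0.77.
- 15-s bins (SD 1.17 × 1.12 = 1.31%): ratios (16 + 1.70)/17.25 = 1.03 and (9 + 1.70)/10.25 = 1.04; power 0.80 and 0.79.

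On the raw-breath reading, power is 0.71 to 0.75 at CV 3% and 0.43 to 0.53 at CV 8%. None of these CVs comes from the documents.

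**5. The offset.** At CV 5% and n = 20, the raw maximum lies about 1.87 × 5 = 9.3% too high. With 10-s bins the bin SD is 5/√(20/3) = 1.94%, so the excess is 0.85 × 1.94 = 1.6%. A change from 25 to 20 breaths in the window moves the raw excess by only 1.965s − 1.867s ≈ 0.1s, or about 0.5% at CV 5%.

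**6. The ramp.** If VO2 still rises by 3.75% over the last 30 s (assumed), the 30-s mean lies 3.75/2 ≈ 1.9% below the end-test value. The raw maximum lies about 7.7% above it (n = 20, CV 5%).

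**The case against.** The strongest reply is that the article never says the maximum is taken over single breaths. It speaks of the highest VO2 value and mentions software processing, so it is compatible with the highest averaged value. An averaging interval is a technical detail that a condensed article may leave to the full protocol. This stands: raw breaths are the literal reading, not a stated fact, and the large ratios depend on it. It does not remove the point, because a maximum over short bins is still noisier than the mean of the window. The loss is then much smaller.

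Second, the rule is identical in every arm and at every visit. This also stands. A reader might infer that the estimated training effect is biased, since training may change breathing pattern. The documents show no such difference, and the shift for a five-breath change is only about 0.1 breath SD. A change in breath-to-breath variability could also shift the offset, but the documents give no figure for it.

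Third, the 30-s mean is not unbiased on a rising ramp. This is correct. It lies slightly below the end-test value, but under the same rule in all arms.

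**Conclusion.** The point holds as a matter of precision. The article defines a primary outcome by a maximum over a 30-s window, and a 30-s mean from the same files would be more repeatable. The ratio of noise SDs is about 2.3 to 2.5 for 20 to 25 independent raw breaths, 1.30 for 10-s bins and 1.17 for 15-s bins. The direction is the same in every variant examined. The size depends on the unstated averaging and on assumed breath counts, breath variability and day-to-day variation.

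A reader might go further and conclude that N = 30 is miscalculated or that the trial is underpowered. The documents do not support that. The figure reproduces under common defaults, and f = 0.25 is a generic effect size not tied to either definition of VO2peak. The power losses shown arise only if that effect size is taken to describe the 30-s mean. Work load, the other primary measure, is untouched. The change is worthwhile and cheap, but the trial's validity does not hang on it.

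**What to change.** Define VO2peak as the mean of all breaths in the last 30 s of loaded exercise, before recovery begins. The highest 30-s rolling mean is an acceptable alternative, but one of the two should be chosen in advance. Compute it from the stored breath-by-breath files with one procedure for all four CPETs and all participants, with group codes concealed. Use the same window for the other variables reported at peak effort. If the software already averages, state the interval.

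The cost is a sentence in the protocol and reprocessing of the stored data. Absolute VO2peak values will be lower than under the present rule and, on a rising ramp, slightly below the end-test value. That applies equally to all arms.

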### Pulmonary function test (PFT)

This examination will be performed according to the international standard [44] and will consist of tests of SVC, FVC and maximal MVV. The test will be performed using a flow module coupled with a system of ventilatory and metabolic measurements (Ultima MedGraphics - St. Paul, MN, USA). The variables to be analyzed are SVC, FVC, FEV_1_, FEV_1_/FVC, IC, ERV and MVV. The predicted values will be calculated according to Pereira [45].

### Protocol for the determination of critical inspiratory pressure (PThC)

An incremental protocol with a load of 50–100% MIP (Fig. 2) will be performed and 10% of MIP will be added every 3 min. The participant will receive a verbal stimulus to maintain the RR at 12 breaths/minute and the test may continue until he reaches 100% of MIP. In this case, if the participant can generate an air flow capable of triggering the equipment more than once at this load, the MIP measurement and the test will be repeated. The following will be considered: failure to maintain the stipulated load at 12 breaths/minute for at least 1 min, failure to maintain respiratory effort indicated by the participant (BORG/CR10 ≥ 7) [35] and the participant requesting interruption. The highest percentage of MIP that the participant is able to maintain for at least 1 min (PTh_MÁX_) will be stipulated as the IME measurement [26–28, 46].

**Fig. 2 Fig2:**
[figure not shown]
Description of steps to calculate critical inspiratory pressure. **a** Incremental inspiratory muscle endurance test. **b** Constant load test. **c** Linear regression to determination of critical inspiratory pressure (PThC). MIP, maximal inspiratory pressure; min, minute; REC, recovery

After determining the PTh_MÁX_, individuals will carry out incursions against a constant load, without the RR being controlled, in order to identify the total time tolerated in each load (T_LIM_). Individuals will be exposed to three different resistances (95%, 100% and 105% PTh_MÁX_) with a 15-min interval between them. The order of resistances will be determined by holding a draw without the individual knowing the order of the charges in which he will be subjected to.

After obtaining the T_LIM_ of each load, a pressure graph will be plotted by time and the PThC will be determined by linear regression between the variables [23].

### Monitoring the experimental protocol

The equipment described subsequently will be used to monitor the participants in the evaluations of the CPET and iIME.

### Metabolic and respiratory variables

The ventilatory and metabolic variables will be collected, breath by breath, through a system of expired gas measurements (Ultima MedGraphics - St. Paul, MN, USA) and processed using specific software (Breeze Suite 7.1, MedGraphics - St. Paul, MN, USA). In addition, the BORG/CR10 scale [35] will be used to assess the participant’s subjective perception of the exercise.

### Cardiovascular variables

The acquisition of the ECG and AP signals to evaluate the cardiovascular responses will be performed at a sampling frequency of 1.000 Hz. The ECG signals will be captured by means of the CM5 lead. The HR will be recorded and stored beat-to-beat. Electrocardiographic signals will be captured and processed via an interface between a bioamplifier for ECG signals (BioAmp FE132, ADInstruments, Australia) and a biological signal acquisition system (Power Lab 8/35, ADInstruments, Australia) and a microcomputer (Intel I5).

On the other hand, pulse pressure will be captured using Finometer Pro® (Finapres Medical Systems, The Netherlands), which allows non-invasive measurements of pulse arterial pressure (FinAP), beat-to-beat, obtained by positioning a cuff on the third phalanx of the third finger of the left hand. The equipment will be calibrated according to the manufacturer’s instructions. In addition to pulse AP, the values of CO, SV and PVR, derived from the AP curves and analyzed using Beat Scope® Easy software (Finapress Medical Systems, The Netherlands) will be evaluated.

### Metabolic evaluation by NIRS

The EI and VL muscle oxygenation variables will be measured by the NIRS (Oxymon Mk III, Artinis Medical Systems, The Netherlands). Two optodes will be used, which will be positioned as described below subsequently: IE = eighth left intercostal space in the anterior axillary line; VL = 12–15 cm of the knee joint, lateral line between the greater trochanter of the femur and the patella [47].

The sampling rate of the device will be set at 250 Hz. Inter-ops distance will be 35 mm for the EI and 40 for the VL [47]. The differential path-length factor (DPF) will be 4 for the EI muscles and 3.83 for the VL. The device will be recalibrated for each subject and the data will be continuously captured during the CPET and the iIME. For each muscle, the change in tissue oxygenation and local blood volume will be estimated by changes in O_2_Hb, HHb and tHb, calculated automatically by the equipment software using the formula (tHB = O_2_Hb + HHb).

### Inspiratory muscle training (IMT)

#### Training description

The training will last for 11 weeks, with a weekly frequency of three sessions and each session will last 1 h. Each session will consist of a 5-min warm up, where each volunteer will perform a constant loading protocol with 50% of their training load. The training protocol will consist of three sets of 15 min of breaths, with a 1-min interval between them (Fig. 3).

**Fig. 3 Fig3:**
[figure not shown]
Schematization of inspiratory muscle training protocol. MIP, maximal inspiratory pressure; min, minute; WU, warm-up

The loads that will be used in the training will be as follows: for the CPG the value of the PThC, for the 60G, the resistance will be 60% of MIP and for the SG, the training will be carried out with a resistance of 6 cmH_2_O. All groups will perform IMT using the linear load respiratory (PowerBreathe inspiratory muscle trainer, Ironman K5, HaB Ltd., UK).

The participants will be instructed to maintain diaphragmatic breathing and RR of 12 breaths/minute for the entire duration of the training protocol, and the RR will be controlled using a recorded verbal command, ensuring that all participants receive the same stimulus. During the 11 weeks of training, participants will be instructed not to change their activities and physical training or food intake.

Every day, before and after the training protocol, the AP will be checked, and the health status of the participants will be observed while the HR is monitored, recorded and stored during all training sessions using a Polar 800CX (Kempele, Finland).

In addition, during the training period, the participants will be asked to complete a physical activity schedule to monitor the activities performed by each individual during the research participation and complete a food survey that will be analyzed later by a nutritionist, thus avoiding these factors interfering with training responses. The weekly training volume and the end, will be controlled over 11 weeks and ensured for all participants throughout this study.

Participants who do not complete the three weekly training sessions and/or the total of 33 training sessions will be excluded during the survey, as will participants who change their physical activities or their eating habits or those who begin to use any supplement or medication continuously.

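### Randomised participants are excluded for incomplete training or changed habits, events the assigned load can influence, so randomisation no longer guarantees a fair comparison of the three groups

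*Protocol article*

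**What the plan says.** In the protocol article, Subjects, allocation is random: "They will be randomly divided into three groups", namely sham (SG), PThC (CPG) and 60% of MIP (60G). Randomisation takes account of aerobic class and age decade.

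Training description sets the dose of training: "The training will last for 11 weeks, with a weekly frequency of three sessions". The last paragraph of that section then gives the rule: "Participants who do not complete the three weekly training sessions and/or the total of 33 training sessions will be excluded during the survey", and continues "as will participants who change their physical activities or their eating habits or those who begin to use any supplement or medication continuously".

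Experimental protocol schedules the exercise and inspiratory tests in weeks 1, 5, 9 and 13. Statistical analysis compares the groups over time with a two-way mixed ANOVA and names no analysis population. It concludes that "at least 30 subjects should participate in this study". Subjects plans that same number: "Thirty recreational male cyclists, aged between 20 and 40 years, will be evaluated".

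**The concern.** Randomisation makes the arms comparable at the moment of allocation. Removing people for what happens afterwards keeps them comparable only if the removal is unrelated to arm or unrelated to outcome. Here it can be related to both.

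- **Attendance.** Completing all sessions can depend on how demanding they are. Each has three 15-minute sets, at 6 cmH2O in one arm and at 60% of MIP or PThC in the others.
- **Change in activity.** The participants are cyclists, and the primary outcomes, VO2peak and workload, are measured on a cycle ergometer. Someone who rides more because training helps, or less because it tires him, could be removed for a consequence of treatment that bears directly on the outcome.

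The article hopes to show that prescribing at PThC gives better results than prescribing at 60% of MIP. How many people can keep to each prescription is part of that question, and a comparison limited to full adherers leaves it out. The balance on aerobic class and age built into the allocation is not protected either.

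**Working it through.** **1. What the attendance rule demands.** 11 weeks × 3 sessions = 33, which is the total in the rule. The required adherence is therefore 100%.

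**2. How many might remain.** The article gives no attendance figures, so this step is assumption only. Let q be the chance that a participant completes a given session, after any rescheduling within the week, independently across sessions. The chance of completing all 33 is q^33.

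| q | q^33 | expected of 30 |
|---|---|---|
| 0.995 | 0.848 | 25.4 |
| 0.99 | 0.718 | 21.5 |
| 0.98 | 0.513 | 15.4 |

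Exclusions for activity, diet, supplements or medication would come on top.

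**3. The plan's sample size.** The stated inputs are f = 0.25, alpha 0.05 and 0.80 (read as power). Three groups follow from the design. The article does not state the number of occasions entered, the correlation between them (rho), or which effect is tested. I assume the group-by-time interaction, m = 4 occasions, rho = 0.5 and sphericity, using the noncentral F:

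- lambda = f² × N × m / (1 − rho) = 0.0625 × 30 × 4 / 0.5 = 15
- df1 = (3 − 1)(4 − 1) = 6; df2 = (30 − 3)(4 − 1) = 81
- power = 0.809

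Searching multiples of three, 30 is the smallest N that reaches 0.80, so the plan's figure reproduces. The match is not unique: a test of the time effect with three occasions and rho = 0.5 also gives 30. Other settings for the interaction give 21 (m = 4, rho = 0.7), 42 (m = 4, rho = 0.3) or 42 (m = 2, rho = 0.5).

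**4. Power if the excluded are not replaced** (same assumptions, same f):

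| analysed | 30 | 29 | 27 | 24 | 21 |
|---|---|---|---|---|---|
| power | 0.809 | 0.792 | 0.754 | 0.688 | 0.610 |

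**5. Bias with no true effect.** Suppose the tendency to complete has correlation r with the outcome, and the lowest fraction p on that tendency is excluded. With normal variables, the mean of those kept shifts by r × φ(z_p) / (1 − p) SD.

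- p = 0.30: 0.3477 / 0.70 = 0.497, so the shift is 0.497 × r
- p = 0.10: 0.1755 / 0.90 = 0.195, so the shift is 0.195 × r
- Between-arm difference: 0.302 × r, which is 0.06 SD at r = 0.2 and 0.15 SD at r = 0.5

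At 40% versus 10% exclusion the range is 0.09 to 0.22 SD. With equal p and the same r in both arms the difference is 0. All values of p and r are assumptions.

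**The case against.** The strongest reply is that the documents contain no evidence that exclusions will be unequal. PThC rests on the idea of a load that can be sustained for a long time. Participants are blinded to their load, which makes arm-related changes in diet or riding less likely. CPG and 60G are both loaded arms, and nothing shows that attendance would differ between them. This stands as a limit on size: the bias is a possibility and cannot be measured from the article. It does not rescue the rule, because concealing the load does not make the sessions equally tolerable.

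A second reply is that analysis sets and missing-data methods belong in a statistical analysis plan, which is not shown, and that a condensed article may omit replacement or follow-up arrangements. This is right about silence. But the article states an affirmative rule that removes people during the study, and no later plan can recover tests that were never done.

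Several stronger readings are tempting but not supported:

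- **Any missed appointment means exclusion.** The rule counts three sessions a week and 33 in total, and does not forbid rescheduling within the week.
- **Any medication or supplement means exclusion.** Only continuous use counts.
- **Data already collected are discarded.** The wording does not say so.
- **The analysed number must fall below 30.** The article gives 30 as a minimum, recruitment was open, and replacement is neither stated nor ruled out.
- **The shift in one arm is the bias.** At 30% exclusion one arm's mean moves by 0.10 to 0.25 SD, but that is the bias in a comparison only if the other arm excludes nobody.

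**Conclusion.** The concern holds as a design fault. The rule acts after randomisation on events that can follow from the assigned load and can bear on the primary outcomes, and the article contains nothing to offset it. Randomisation therefore no longer guarantees comparability. A reader might infer that the result will be biased or the randomised basis destroyed; the documents do not support that.

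The size is unknown. The illustrative between-arm shift is 0.06 to 0.15 SD at 30% versus 10% exclusion with a correlation of 0.2 to 0.5, and about 0 when exclusion and mechanism are equal.

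Loss of power is conditional. Without replacement, and with four occasions and rho = 0.5, a single exclusion takes power just under 0.80 (0.79 at 29), and nine take it to 0.61. With rho = 0.7, 21 participants would still reach 0.80. Replacement would restore the number but leave the selection in place.

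**What to change.** Replace the exclusion rule with one that separates deviating from training from leaving the study:

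- Invite every randomised participant to the tests already scheduled at weeks 5, 9 and 13, whatever his attendance, activity, diet, or supplement or medication use, unless he withdraws consent or testing is precluded for health reasons.
- For the primary comparison, analyse all randomised participants in the arm allocated, with a likelihood-based mixed model that uses participants who have a missing visit.
- Report attendance and each kind of deviation by arm.
- Keep the full-adherence set only as a labelled per-protocol sensitivity analysis.

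The cost is a change of wording in the protocol and analysis plan, plus scheduled test visits for people who would otherwise have been dropped. The downside is that non-adherence may somewhat dilute the estimated effect. No training load or clinical rule needs to change.
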